We previously demonstrated that exertional dyspnea measured with the Medical Research Council dyspnea score (MRCDS), lung function and 6-min walk distance (6MWD) are significant and independent predictors of survival in IPF, with no observed collinearity among them [8]. The independence of the 3 domains (dyspnea, lung function, exercise capacity) was demonstrated in a prospective study [3] and in a multi-centre study as well [9].

The Risk Stratification Score (RISE) was first developed in a cohort of patients with IPF who were prospectively followed, and tested in another, retrospectively enrolled cohort. The acronym was later changed from ROSE to avoid confusion with “rapid onsite evaluation”. Capturing each of the 3 aforementioned domains, RISE is based on MRCDS, Composite Physiologic Index (CPI) and 6MWD. RISE was demonstrated to be superior to individual variables in predicting LTx-free survival [3]. We subsequently demonstrated that RISE was a reliable predictor of mortality in patients assessed for LTx [9], and also able to capture patient response to anti-fibrotic therapy better than the commonly used variables [11]. However, the main limitations of the 2012 study were the size of the prospective cohort, and the lack of prospective validation.

The current approach to the detection of progression of disease in IPF is largely based on forced vital capacity (FVC) changes and high-resolution chest CT scan (HRCT). We recently demonstrated that the prognostic accuracy of a decline of FVC combined with an increase of the extent fibrosis on HRCT (visual score) is far from being optimal, although the 2 variables are independent from each other [12]. This finding further strengthens the rationale for pursuing the development and validation of an integrated, multi-dimensional prognostic tool for IPF. As a more recent development, we tested a modified version of CPI against the original one, and found the new CALIPER-based CPI to be a stronger predictor of survival in IPF [13], making it a candidate component of the RISE.

The main objective of the study is to test and validate a modified version of the RISE in 2 separate cohorts of patients with IPF, prospectively followed from the time of diagnosis. To our knowledge, no previous, large scale, prospective, 3-year observational study has been conducted to validate a multi-dimensional staging system for IPF.

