We hypothesize that both RISE at baseline and its longitudinal changes are the best predictors of survival in patients newly diagnosed with IPF followed for a period of 3 years, both in terms of sensitivity and specificity. The prognostic power of RISE will be compared to the current standard of care (individual pulmonary function tests, 6MWD, HRCT chest scan fibrosis score) and with other multi-dimensional scores as well, namely Gender-Age-Physiology (GAP) Index [14], CPI (both original and CALIPER-revised versions) [15, 16] and Mortality Risk Scoring System (MRSS) [17].

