At the end of the study period, both baseline RISE and longitudinal changes of RISE will be tested as predictors of mortality. Other individual variables will also be tested as predictors of mortality, including age at the time of diagnosis, time between onset of symptoms and diagnosis (months), gender, body mass index, smoking history (pack-years), FVC, DLCO, 6MWD (meters and % predicted), desaturation during 6-min walk test, HRCT visual fibrosis score at the time of diagnosis, and other multi-dimensional scores (GAP, CPI, MRSS). In the validation cohort, we will seek to confirm and validate results obtained in the development cohort.

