### Statistical analysis and sample size calculation

The distribution of variables considered will be analysed with Kolmogorov–Smirnov test. Interobserver variability among chest radiologists and lung pathologists will be assessed with Weighted kappa coefficients [29]. Survivors and non-survivors will be compared by using the unpaired t-test, or, for not normally distribute variables, with the Mann–Whitney U-test. To rule out multicollinearity and demonstrate that included variables are truly independent, variance inflation factors of the RISE components will be calculated [30]. Receiver operating characteristics analysis will be used to identify the most accurate cut-off values for each variable to predict endpoints. Multivariate analysis of significant predictors of endpoints will be conducted with the Cox proportional hazard model. Results will be summarized as hazard ratios. Once patients are listed for LTx, death and LTx become competing events. To account for the competing risks of LTx and death in the population of patients undergoing LTx assessment, the Fine-Gray competing risk regression model [31] will be used. This will identify variables significantly predicting independent survival status and results will be summarized as subdistribution hazard ratios. These represent the relative risk of dying prior to LTx. Survival will be further evaluated using Kaplan–Meier curves and the log-rank test. Sample size calculation for an observational, cohort study was conducted using the methodology described by Wang and Ji [32], with the assistance of a statistician. Using available, preliminary data on 109 patients, dropout rate, ratio of low RISE to high RISE, and mortality rates in low RISE and high RISE subgroups were determined. With a power (probability of detecting a real effect) of 90%, and with a conservative approach, a sample size of 125 patients for each cohort was determined to be required.

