The purpose of our study is to validate a multi-dimensional index prospectively and with a period of observation (3 years) more than adequate to capture significant progression of disease and mortality. Inclusion criteria will be rigorous, with a panel of chest radiologist and lung pathologists with ILD expertise assessing each case. An important aspect of this study will be the assessment of longitudinal changes of RISE as a reliable predictor of survival, as well as the assessment of performance across a wide range of disease severity, as this will ensure clinical reproducibly of this tool in a variety of clinical scenarios. The inclusion of 2 separate cohorts will ensure that results are indeed validated. While our primary objective is to validate a clinical tool for staging and clinical decision making, secondary endpoint measures will generate a wide array of clinically relevant information.

In conclusion, it is our hope that the current study will establish RISE as a straightforward, inexpensive, easily obtainable, reproducible, and reliable tool for clinical decision making in patients with IPF.

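### Validation of RISE is the main objective, but the analyses and sample-size basis written down test association, so significance in the second cohort would often not show that performance was retained

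*Protocol article*

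**What the plan says.** The Background section states the purpose: "The main objective of the study is to test and validate a modified version of the RISE in 2 separate cohorts". The abstract gives the intended use as guiding clinical decisions and possibly serving as a trial endpoint.

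On how validation is to be judged, Methods and design offers one sentence: "In the validation cohort, we will seek to confirm and validate results obtained in the development cohort". The Discussion goes further: "The inclusion of 2 separate cohorts will ensure that results are indeed validated".

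The section on statistical analysis and sample size gives ROC analysis one job: "Receiver operating characteristics analysis will be used to identify the most accurate cut-off values for each variable to predict endpoints". The footnote to Table 2 says the same. The remaining outcome analyses are comparisons of survivors with non-survivors, Cox and Fine-Gray models summarised as hazard ratios, and a group comparison: "Survival will be further evaluated using Kaplan–Meier curves and the log-rank test". Sample size rests on mortality in low- and high-RISE subgroups from preliminary data on 109 patients, with 90% power: "a sample size of 125 patients for each cohort was determined to be required".

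Discrimination appears in the Background hypothesis, where RISE is expected to be the best predictor "both in terms of sensitivity and specificity", and in a stated intention: "The prognostic power of RISE will be compared to the current standard of care". Neither statement is tied to an estimate, a test or a margin in the validation cohort.

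**The concern.** A log-rank test or a hazard ratio in the validation cohort asks whether RISE has any association with survival. Validation asks a different question: whether the performance seen in development holds in new patients, at a level that supports decisions on treatment and transplant referral. A score can lose much of its discrimination and still be associated with survival.

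Some loss is foreseeable. The cut-offs are to be chosen by ROC analysis, and the modified version goes forward only if it beats the older one. Both are data-driven choices that tend to flatter the development cohort. If the second cohort is then read mainly through tests of association, a clearly weaker score could be reported as confirmed.

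**Working it through.** **Inputs.** From the article: 125 patients per cohort, 90% power, 3 years of follow-up, a four-level score (0 to 3, Table 2), sizing on low- versus high-RISE mortality. The article does not give alpha, the two mortality rates, the low:high ratio or dropout. These are assumed below and varied. The low/high split at 0–1 versus 2–3 is also assumed.

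**1. The article's own figure.** 125 can be neither confirmed nor refuted without those inputs, but it is compatible with many. Example at two-sided 5% and 90% power, 30% versus 60% mortality, 1:1, mean 0.45:

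n per group = [1.96·√(2·0.45·0.55) + 1.282·√(0.3·0.7 + 0.6·0.4)]² / 0.30² = (1.379 + 0.860)² / 0.09 = 55.7, so 56. The total is 112, and with 10% dropout 112/0.9 = 124.4, so 125.

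Likewise 25% versus 55% with 40% high RISE and 10% dropout gives 125.

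**2. What a significant low/high difference means as discrimination.** For a two-group score, AUC = (sensitivity + specificity)/2. Take 125 analysed, half high RISE, overall mortality 40%:

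- Standard error of the difference = √(0.4·0.6·4/125) = 0.0876. The difference that is just significant is 1.96·0.0876 = 0.172, that is 31.4% versus 48.6%.
- Sensitivity = 0.5·0.486/0.4 = 0.608; specificity = 0.5·0.686/0.6 = 0.572; AUC = 0.59.
- At 90% power the difference is 26% versus 54%: sensitivity 0.675, specificity 0.617, AUC about 0.65.

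Over 30–50% mortality and 30–50% high RISE, these AUCs run about 0.58–0.60 (just significant) and 0.63–0.66 (90% power).

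On the hazard-ratio scale, HR = exp[z/√(D·π(1−π))], with D events and π the high-RISE share. With D = 50 and π = 0.5: exp(1.96/3.536) = 1.74 just significant, and exp(3.242/3.536) = 2.50 at 90% power. Over 38–63 events and π of 30–50% the ranges are about 1.6–2.0 and 2.3–3.2.

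**3. Chance of significance for a degraded score.** Simulated exponential survival, 125 patients, 3 years, two-sided 5%.

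First set of assumptions: RISE 0/1/2/3 in 30/30/20/20%, 5% dropout per year, 50–70% three-year event-free survival. HR 2.5 per point gives C about 0.75 (3-year AUC 0.80–0.82). HR 1.5 gives C about 0.62 (AUC 0.65–0.67).

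- HR 1.5: low/high log-rank significant in 66–87% of cohorts. A Cox trend in RISE is significant in 77%, 86% and 93% at 70%, 60% and 50% survival.
- HR 1.4 (C about 0.60): log-rank significant in 52–71%.

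Second set: shares 25/30/25/20%, 10% dropout, log-rank 0–1 versus 2–3:

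| HR per point | C | 70% survival | 60% | 50% |
|---|---|---|---|---|
| 1.4 | 0.60 | 48% | 59% | 68% |
| 1.5 | 0.62 | 59% | 73% | 84% |
| 1.6 | 0.64 | 74% | 86% | 92% |
| 1.8 | 0.67 | 90% | 96% | 99% |
| 2.5 | 0.74 | >99% | >99% | >99% |

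**4. What 125 patients can say about C directly.** The sampling SD of C is about 0.03–0.05, so a 95% interval is roughly ±0.06 to ±0.10. As an example criterion, take a lower 95% bound above 0.60. With SD 0.037 (60% survival), 90% power needs a true C of 0.60 + (1.96 + 1.28)·0.037 = 0.72. At true C 0.70 the power is about 64–84% across the survival range. At C 0.62 fewer than 10% of cohorts would meet it.

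**The case against.** The strongest reply is that this is mostly an omission. A journal article condenses its statistics, and a C-index with its interval, a threshold, optimism correction and calibration are normal content for a full protocol or analysis plan. That stands for the detail, and the missing detail alone is not the point. What remains is what the article does fix: a main objective of validation, a sample size tied to a group difference, ROC confined to cut-offs, and a statement that two cohorts guarantee validation. That last statement is Discussion wording, and the Methods sentence is more modest, but no design can guarantee the result.

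Four stronger readings are tempting and not supported:

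- *That validated simply means significant again.* The article never says so. It states no other rule, which is different. The alpha and the low/high split used above are assumptions.
- *That no performance measure is mentioned.* The Background names sensitivity and specificity and a comparison with other scores, and a degraded RISE could fail that comparison. No estimate, test or margin is attached to it.
- *That RISE cannot fail.* The simulations contradict this. The log-rank misses significance in roughly 13–34% of cohorts at C about 0.62 and 29–48% at C about 0.60 under the first assumptions, and in up to 52% at C 0.60 under the second.
- *That 125 is wrong.* It is reproducible from plausible inputs.

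It is also fair to object that a pass mark of 0.60 has no basis in the documents and costs power. It is offered below only as an illustration.

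**Conclusion.** The point holds in limited form. The analyses and the sample-size basis in the article address association, while the main objective is retained performance. With 125 patients, a fall in C from about 0.75 to about 0.62 would still leave a significant low/high log-rank in roughly 66–87% of cohorts (59–84% under the second set of assumptions). At C 0.60 the figure is about half to 70%. A significant result in the second cohort would therefore often not distinguish a score that held up from one that weakened clearly.

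These percentages rest on assumed alpha, survival, score distribution, dropout and proportional hazards per RISE point. Whether C 0.62 is clinically adequate is a judgement the documents do not settle. This should be changed, but it does not invalidate the design.

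**What to change.** In the last paragraph of Methods and design before the primary endpoint, and in the statistics section:

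1. State that the RISE version, cut-offs and scoring chosen in development are applied unchanged in the validation cohort.
2. Make the primary validation result a censoring-aware C-index or 3-year time-dependent AUC of that score, with its 95% CI. Report alongside it the change from the optimism-corrected development value, and observed versus predicted 3-year risk by RISE level.
3. Judge validation on that estimate against a minimum the sponsor fixes before validation data are opened. A lower bound above C 0.60 is one example, and its power cost (step 4 of the working) should be weighed before it is adopted.
4. Keep hazard ratios and the log-rank test as supportive, and state the alpha.
5. In the Discussion, replace "The inclusion of 2 separate cohorts will ensure that results are indeed validated" with wording that the second cohort tests whether the results hold.

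Cost: wording and a little more analysis of data already being collected, with no added patients for the estimate itself. The downside is a validation claim that can fail, and a demanding minimum may be underpowered at 125.

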### Primary endpoint

Three-year, LTx-free survival from the time of diagnosis, measured as the time between diagnosis and death from any cause, or LTx. Once they receive a LTx, patients will be censored. Since mortality and LTx are competing events, a Fine-Gray competing risk regression analysis will be used. Please refer to the statistics section for details.

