## Discussion

IPF is a condition associated with a poor prognosis [2–4], but clinical deterioration occurs with rather difficult to predict patterns. Many deaths in IPF occur due to subacute respiratory deterioration [4], with a slow decline in lung function. Nevertheless, approximately 30% of the patients die because of AEs, while infection, pulmonary embolism, heart disease, and lung carcinoma have a significant impact on the evolution of the disease in individuals affected by IPF as well [4]. Anti-fibrotic agents pirfenidone and nintedanib have shown to slow the disease course [6, 33], but LTx remains the only definitive treatment for this disease, associated with significantly improved survival [34].

In this context, clinical decision making on therapy start and switch has a direct impact on survival. It is also equally important not to miss the LTx window, when patients are still eligible for transplant. This is particularly challenging when navigating a lengthy assessment process with a condition that can be rapidly progressive. Not surprisingly, LTx waitlist mortality is the highest among patients with IPF [35]. As a result, clinical tools able to detect clinically significant progression and predict the prognosis in individual patients are paramount in IPF.

In this observational, prospective trial, RISE will be tested as a candidate staging system for IPF to be used in day-to-day clinical decision making. RISE is designed to be straightforward, easy to obtain and repeat, inexpensive and entirely managed by the pulmonary specialist. The 3 domains captured by RISE are exertional dyspnea, exercise capacity and lung function. The prognostic independence between the 3 domains has been demonstrated [3].

As in all chronic lung diseases, IPF impacts patients’ quality the life with disabling symptoms (i.e., dyspnea and cough) and with functional impairment in everyday life. As far as dyspnea perception is concerned, several scales have been utilized. Among them, an increase of MRCDShas shown good correlation with quality-of-life impairment [36, 37] and mortality [38] in patients with IPF.

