The Gender-Age-Physiology (GAP) index considers gender, age, FVC (% predicted) an DLCO (% predicted) to stratify patients in 3 different stages of the disease. This model was validated with a 3-year retrospective study using 3 different cohorts (558 patients), and it was shown to predict mortality in patients with IPF [4]. However, 3 different studies demonstrated that longitudinal changes of GAP performed poorly in predicting survival [11, 46, 47]. The use of (relatively) fixed variables such as gender and age and the lack of prospective validation may explain these limitations.

The MRSS with Ascertainable Predictors (accounting age, history of respiratory hospitalization, FVC [% predicted] and 24-week change in % predicted FVC), was studied in a 1-year prospective clinical trial with 830 participants [17]. A longer follow-up will be needed to adequately capture mortality in IPF. A potential concern in this score is the use of hospitalization as a parameter, given that criteria for hospital admission vary in different institutions, potentially compromising reproducibility.

An encouraging finding was that multi-dimensional indices (RISE, CPI and GAP) proved their effectiveness even in patients undergoing LTx assessment [9], with an accuracy in predicting mortality similar to the Lung Allocation Score, which is commonly used to evaluate patients on LTx waiting lists, but is much more complex to calculate [48, 49].

The use of multi-dimensional indices as clinical trials endpoints is another, crucially important, potential application of multi-dimensional indices. The search for new therapies in IPF in the immediate future will be particular challenging, as most treatments are only able to slow down an occurring progression of disease, making it very difficult to capture a clinically significant difference. This further points to the limitations of FVC decline as only endpoint measure, and, at the same time, to the advantage of using parameters that better capture pathophysiology and clinical status in IPF, but are still easily repeatable. A preliminary study on RISE as a parameter to longitudinally capture response to pirfenidone indeed yielded encouraging results [11].

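### The primary endpoint handles lung transplantation in three incompatible ways, and the choice can change how RISE ranks against the age-containing scores GAP and MRSS

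*Protocol article*

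**What the plan says.** The Primary endpoint section of the protocol article contains three statements about LTx, one after the other:

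- It is part of the endpoint: "Three-year, LTx-free survival from the time of diagnosis, measured as the time between diagnosis and death from any cause, or LTx".
- It is censored: "Once they receive a LTx, patients will be censored".
- It is a competing event: "Since mortality and LTx are competing events, a Fine-Gray competing risk regression analysis will be used".

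That section refers to the statistics section for details. There the scope is narrower: "To account for the competing risks of LTx and death in the population of patients undergoing LTx assessment, the Fine-Gray competing risk regression model" is to be used. Of the resulting subdistribution hazard ratios it says: "These represent the relative risk of dying prior to LTx". Otherwise the statistics section plans ROC analysis for cut-offs, Cox regression for predictors of the endpoints, and Kaplan-Meier curves with log-rank tests. It does not say how LTx enters any of these.

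The target of prediction also varies. The hypothesis at the end of the Background is that RISE and its changes predict survival best, in sensitivity and specificity. Methods and design tests RISE, GAP, CPI and MRSS as predictors of mortality. The first secondary endpoint compares RISE as a predictor of LTx-free survival.

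The comparison is to be made with single tests and "with other multi-dimensional scores as well, namely Gender-Age-Physiology (GAP) Index", CPI and MRSS. The Discussion lists age among the components of both GAP and MRSS. RISE is built from the MRC dyspnea score, 6-minute walk distance and CPI.

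**The concern.** The three handlings answer different questions. If LTx is part of the endpoint, it cannot also compete with it or be censored. If LTx is censored, the patient leaves the risk set at transplant; under Fine-Gray the patient stays in it.

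This need not be harmless for a ranking of scores. Older age raises the risk of death. If transplants go mainly to younger patients, older age also lowers the chance of LTx. On a death-or-LTx composite the age points of GAP and MRSS would then be partly cancelled, while a score without an age term would lose little. On death before LTx the effect would be absent or opposite. The headline claim for RISE could therefore depend on a choice the article has not settled, and on the transplant rate at each centre.

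**Working it through.** **1. The plan's own figures.** The article gives no LTx rate, no age distribution of transplanted patients and no expected c-index, so there is no planned figure to reproduce on this point. The sample size of 125 per cohort bears only on precision.

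**2. What each handling means for a transplanted patient.**

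| Statement in the article | Role of LTx | What is predicted |
|---|---|---|
| Endpoint definition | failure | death or LTx |
| Next sentence | censored at LTx | death, cause-specific |
| Sentence after that | competing event, all patients | death before LTx |
| Statistics section | competing event, assessed patients only | death before LTx in that subset; unstated for the rest |

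**3. Simulation of the three handlings (all inputs assumed).** Age, physiology and exercise are independent standard normal variables.

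- Death hazard = 0.13 × exp(0.5·age + 0.5·phys + 0.4·ex) per year.
- LTx hazard = r × exp(−1.0·age + 0.3·(phys + ex)), a hazard ratio of exp(−1.0) = 0.37 per SD of age.
- Age-containing score = 0.5·age + 0.5·phys. Age-free score = 0.5·phys + 0.4·ex.
- Four sets of 6,000 patients, capped at 3 years; Harrell's C.
- Fine-Gray-type handling keeps transplanted patients at risk to the end, without an event.

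Entries are C(age-free) minus C(age-containing):

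| LTx share | Death if no LTx occurred | LTx as failure | LTx censored | Fine-Gray-type |
|---|---|---|---|---|
| 4% | −0.020 | +0.007 | −0.019 | −0.024 |
| 8% | −0.019 | +0.030 | −0.018 | −0.030 |
| 18% | −0.017 | +0.076 | −0.014 | −0.040 |
| 8%, LTx unrelated to age | −0.019 | −0.005 | −0.020 | −0.023 |

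Shift = entry minus the no-LTx column:

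- LTx as failure: +0.007 + 0.020 = 0.027 at 4%; +0.030 + 0.019 = 0.049 at 8%; +0.076 + 0.017 = 0.093 at 18%. The ranking reverses each time.
- LTx censored: at most −0.014 + 0.017 = 0.003. The ranking is kept.
- Fine-Gray-type: −0.024 + 0.020 = −0.004, −0.030 + 0.019 = −0.011, −0.040 + 0.017 = −0.023. This favours the age-containing score.
- LTx unrelated to age: −0.005 + 0.019 = 0.014 on the composite, with no reversal. This remainder arises because LTx in the model follows severity.

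**4. A second model, to vary the assumptions.** Age ~ N(70, 8), severity ~ N(0, 1), 5,000 patients per setting.

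- Death hazard = 0.18 × exp(0.6·severity + b·(age − 70)), with b = 0.02, 0.03, 0.04. The hazard ratio per 10 years is exp(0.2) = 1.22 to exp(0.4) = 1.49.
- LTx hazard = r × exp(0.8·severity) under age 70 and zero from 70, with r = 0.03, 0.06, 0.12.
- The RISE-like score is severity plus noise (SD 0.7) in four levels. The comparator is severity plus noise plus w·(age − 70)/8, with w = 0.4, 0.7, 1.0.

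This gives nine settings per LTx rate. Two runs with different seeds and cut-points gave these shifts from death with LTx censored to the composite:

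| LTx share | Shift towards age-free score | Reversals of nine |
|---|---|---|
| 4% | 0.007 to 0.017 | 1 to 2 |
| 7 to 8% | 0.010 to 0.033 | 2 to 3 |
| 13% | 0.016 to 0.058 | 6 to 8 |

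**The case against.** A reader might infer from the definition sentence that the endpoint is simply tilted towards RISE. The article does not support that. LTx as a failure is only one of its three handlings; under the other two the tilt disappears or favours the age-containing scores. Methods and design also tests the scores as predictors of mortality, which is close to a comparison on death.

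The age gradient is not in the article either. The Discussion says only: "It is also equally important not to miss the LTx window, when patients are still eligible for transplant". The second model's cut at age 70 is extreme.

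The comparator's lead on death is partly built in, because it stays continuous while the RISE-like score has four levels. The Discussion describes GAP as having three stages. With the comparator cut to three, the difference on death shrinks to about −0.02 to +0.01, although the composite shift remains. With 125 patients the c-index difference has a standard deviation of about 0.04 in simulation, so most of the shifts are smaller than chance variation in one cohort.

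Death or LTx is also a defensible target for a tool meant to guide referral, and comparisons by age and site are already planned.

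These points limit the size and direction of what can be claimed. They do not remove the contradiction. Fine-Gray is confined to assessed patients, and ROC and Cox are applied to endpoints whose definition includes LTx. A simple 3-year ROC must also class each transplanted patient as event or non-event.

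**Conclusion.** The point holds as an unresolved contradiction with a possible effect on the headline ranking. It does not establish that the trial is biased towards RISE.

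The contradiction is certain from the text. Its effect is conditional on LTx going mainly to younger patients. Then, at assumed LTx shares of 4 to 13%, counting LTx as a failure moves the c-index difference towards an age-free score by roughly 0.01 to 0.05 and reverses the ranking in some settings. Censoring removes the shift. Fine-Gray-type handling moves it towards the age-containing scores, by 0.004 to 0.011 at 4 to 8% LTx. The simulations show direction and rough size, not this trial's actual bias.

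The argument reaches GAP and MRSS only, not CPI or the single tests. RISE may carry some age indirectly through percent-predicted values. The point should be settled before the scores are compared.

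**What to change.** 1. State one handling of LTx, apply it to every score in the whole cohort, and bring the hypothesis, the mortality analysis in Methods and design, the primary endpoint, the first secondary endpoint and the statistics section into line with it.
2. Make the RISE-versus-GAP and RISE-versus-MRSS comparisons on death, with LTx censored. Because such censoring may depend on age and severity, add a sensitivity analysis with inverse-probability-of-censoring weights from both.
3. Report the death-or-LTx composite beside it, so that any dependence of the ranking on LTx is visible.
4. Call RISE the best predictor of survival only if it also leads on death.

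The cost is wording and one extra model per comparator. No new data are needed, since deaths and transplants are already recorded. The death analysis has somewhat fewer events than the composite, so its intervals will be slightly wider.

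### The primary endpoint counts lung transplantation as an event, as censoring and as a competing event, and the statistics section does not settle which applies

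*Protocol article*

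**What the plan says.** The *Primary endpoint* section gives transplant three roles in successive sentences.

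- **Event.** Three-year LTx-free survival is "measured as the time between diagnosis and death from any cause, or LTx".
- **Censoring, then competing event.** "Once they receive a LTx, patients will be censored. Since mortality and LTx are competing events, a Fine-Gray competing risk regression analysis" is to be used. No subpopulation is named here, and the reader is sent to the statistics section for details.

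The *Statistical analysis and sample size calculation* section then says the following.

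- "Multivariate analysis of significant predictors of endpoints will be conducted with the Cox proportional hazard model", without saying how transplant is coded.
- Fine-Gray is introduced for a narrower group: "To account for the competing risks of LTx and death in the population of patients undergoing LTx assessment". Death and transplant are said to compete from the time of listing.
- Of the subdistribution hazard ratios it says: "These represent the relative risk of dying prior to LTx".
- Kaplan–Meier curves and the log-rank test are added, again with no coding of transplant.
- The 125 patients per cohort rest on mortality rates in the low- and high-RISE groups.

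Elsewhere in *Methods and design*, "both baseline RISE and longitudinal changes of RISE will be tested as predictors of mortality". There the outcome is death, not death or transplant.

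**The concern.** The three roles answer three different questions: how RISE relates to death or transplant, to the rate of death among patients not yet transplanted, and to the cumulative incidence of death before transplant. They use different event counts and different risk sets, and can give different hazard ratios from the same patients.

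This is the primary endpoint of a study meant to validate a score, and the coding reaches further than the final model. Cut-offs for the RISE components are chosen by ROC analysis against the endpoints. A patient transplanted within three years may be a case, a non-case or excluded there, so the coding can affect how the score is built. The comparison of survivors with non-survivors has the same gap. If the rule is settled only after the data are seen, the choice can be influenced by the results.

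**Working it through.** **1. Can the stated rules all be followed?**

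- If transplant is part of the event, a transplanted patient has had the primary event. Nothing is left to censor or to compete.
- If transplant is ordinary censoring, the patient leaves the risk set at transplant without an event.
- If transplant competes under Fine-Gray, the patient has no event of interest but stays in the subdistribution risk set. That is not ordinary censoring.

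These exclude one another. The statistics section adds a second model (Cox), a narrower Fine-Gray population (patients assessed for transplant) and a later start of competition (listing), whereas the endpoint runs from diagnosis in all patients.

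**2. The plan's own figure.** The 125 per cohort at 90% power cannot be reproduced: the article gives no values for the mortality rates, RISE ratio or dropout, and no alpha. The point does not depend on it.

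**3. Size under assumed hazards.** The protocol gives no hazards, so all of these are assumptions. Let d be the yearly death hazard and t the yearly transplant hazard, constant over 3 years, with subscript 0 for low RISE and 1 for high RISE.

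- Composite HR = (d1 + t1)/(d0 + t0)
- HR with transplant censored = d1/d0
- Cumulative incidence of death before transplant: CIF = d/(d + t) × (1 − exp(−3(d + t)))
- Approximate subdistribution HR = ln(1 − CIF1)/ln(1 − CIF0)

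Throughout, d0 = 0.10 and d1 = 0.30, so the transplant-censored HR is 0.30/0.10 = 3.0.

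| t0, t1 | Composite HR | CIF0, CIF1 | Approx. subdistribution HR |
|---|---|---|---|
| 0.02, 0.10 | 0.40/0.12 = 3.33 | 0.252, 0.524 | 2.56 |
| 0.02, 0.20 | 0.50/0.12 = 4.17 | 0.252, 0.466 | 2.16 |
| 0.05, 0.05 | 0.35/0.15 = 2.33 | 0.242, 0.557 | 2.95 |
| 0.005, 0.015 | 0.315/0.105 = 3.00 | 0.257, 0.582 | 2.93 |

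The order of the three results changes with the transplant pattern. When transplant is more frequent in high RISE (rows 1 and 2), the composite is the largest and the subdistribution HR the smallest. When it is unrelated to RISE (row 3), the composite is the smallest. When it is rare (row 4), the three nearly coincide.

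Rows 1 and 2 imply that 0.10/0.40 × (1 − exp(−1.2)) = 17% and 0.20/0.50 × (1 − exp(−1.5)) = 31% of high-RISE patients are transplanted by 3 years.

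**4. Check of the approximation.** Solving the large-sample Fine-Gray score equation, with d = 0.10 and 0.25 and t = 0.05 and 0.15, gives a composite HR of 2.67, a censored HR of 2.50 and a subdistribution HR of 2.11. The ordering matches rows 1 and 2.

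**5. Events.** Under the hazards of step 4, with 125 patients split 1:1 by RISE and no dropout, the 3-year probabilities of death before transplant are 0.242 and 0.437, and those of transplant are 0.121 and 0.262. Expected deaths before transplant are 62.5 × (0.242 + 0.437) ≈ 42. Expected composite events are 62.5 × (0.242 + 0.121 + 0.437 + 0.262) ≈ 66. The event definition therefore also matters for what the 125 can support.

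**The case against.** The strongest reply is that the text leans one way. The *Primary endpoint* section names one method, Fine-Gray. The statistics section gives the matching quantity, death before transplant. The statement on testing RISE and the sample size inputs both speak of mortality, and censoring may mean only that follow-up stops at transplant. On that reading the odd items are the composite wording, the LTx-free label, the Cox sentence and the restriction of Fine-Gray to assessed patients. This has force: a reader might infer that the analysts are free to choose among three equal primary results, and the document does not go that far. The conflict remains, because the favoured reading still contradicts the endpoint's own definition and the stated Fine-Gray population.

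Other stronger inferences are not supported either.

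- **High-RISE patients are transplanted more often.** The article gives no transplant rate by RISE. Its *Discussion* warns that patients can miss the period in which they are eligible, so even the direction is uncertain.
- **The Kaplan–Meier curves will overstate mortality.** If they censor at transplant, one minus Kaplan–Meier for high RISE is 1 − exp(−0.9) = 59%, against a cumulative incidence of 52–47% in rows 1 and 2. But the coding in the curves is not stated.
- **The Fine-Gray analysis is biased because patients must survive to assessment.** That depends on its time origin, which is not stated. For the secondary endpoint on listed patients, counting from listing would be legitimate.

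A missing analysis plan does not answer the point. The article states the endpoint, the censoring rule and the model, and these statements disagree.

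**Conclusion.** The concern holds as a contradiction in the stated text, and it should be corrected because it concerns the primary endpoint. The primary RISE effect has no single definition: a Cox hazard ratio and a subdistribution hazard ratio both stand, in different populations, and the event is death in some places and death or transplant in others.

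This conclusion needs no assumption about hazards. The numerical effect does. In the assumed cases it runs from negligible when transplant is rare to a composite HR of 4.2 beside a subdistribution HR of 2.2 when transplant is frequent and concentrated in high RISE. The documents do not show where in that range this study lies. Calling the subdistribution hazard ratio a relative risk is loose terminology and a minor matter.

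**What to change.** Choose one primary estimand, in all enrolled patients from diagnosis. Either choice removes the contradiction.

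- **Option A, the named composite.** Death and transplant both count as events, analysed by Cox and Kaplan–Meier. Delete the censoring and Fine-Gray sentences from *Primary endpoint*. This changes the endpoint's label least, but departs from the mortality wording in *Methods and design* and the sample size inputs.
- **Option B, death before transplant.** Transplant is a competing event, analysed by Fine-Gray with cumulative incidence curves. Remove transplant from the event definition, revise the LTx-free label, and drop the restriction to patients assessed for transplant.

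Report the other estimand as secondary. Then align *Primary endpoint*, the statement on testing RISE in *Methods and design*, and the statistics section. State the same transplant coding for the ROC step, the survivor/non-survivor comparison and the Kaplan–Meier curves. Say whether the 125 per cohort rests on deaths or on deaths plus transplants. Reword the sentence interpreting the subdistribution hazard ratio.

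The cost is wording changes in these sections and one extra secondary model. Deaths and transplants are already recorded, so no new data are needed.
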